#### ④ Specialized Chuna techniques for complex malposition

- **Extension + rotation + ipsilateral lateral bending malposition – side-lying trunk lever thrust technique**

- *Patient position:* Side-lying with the involved side downward.
- *Physician position:* Standing in a fencing stance in front of the patient.
- *Contact:*
  - Main hand (foot-side hand): the forearm contacts the iliac crest of the pelvis on the lower side.
  - Assisting hand (head-side hand): the forearm contacts the axillary region of the upper shoulder and supports the trunk.
- *Correction:*
  - The trunk is rotated toward the correction direction by guiding the shoulder with the assisting forearm, while the main forearm on the ilium induces posterior rotation of the pelvis relative to the trunk.
  - After preloading the tissues and confirming motion at the involved segment, the physician delivers a quick thrust using body weight, pulling the ilium anterosuperiorly or anteroinferiorly (depending on the pattern) to correct the extension-rotation-lateral bending malposition.
- **Flexion + rotation + ipsilateral lateral bending malposition – side-lying trunk lever thrust technique**
  - *Patient position:* Side-lying, with leg and trunk positioning adjusted to emphasize flexion at the target segment.
  - *Physician position:* As above (fencing stance in front of the patient).
  - *Contact:* Main forearm on the iliac crest; assisting forearm at the axilla.
  - *Correction:*
    - The trunk is rotated and flexed to localize motion at the involved segment.
    - The physician then applies a rapid thrust through the ilium using the main forearm while stabilizing the trunk with the assisting forearm, thereby correcting the flexion-rotation-lateral bending malposition.
- **Lateral bending with contralateral rotation malposition – side-lying trunk lever thrust technique**
  - *Patient position:* Side-lying, with the lower trunk slightly flexed or extended and the legs positioned to emphasize the lateral bending component.
  - *Physician position:* Standing in front of the patient in a fencing stance.
  - *Contact:*
    - Main forearm on the iliac crest of the lower side.
    - Assisting forearm at the axillary region of the upper side.
  - *Correction:*
    - The assisting forearm induces controlled rotation of the trunk, while the main forearm applies a thrust through the pelvis in the opposite direction of the malposition.
    - Using body weight, the physician performs a momentary thrust at the end range of combined motion to correct the lateral bending + contralateral rotation pattern.
-

## 6. Inclusion criteria, exclusion criteria, target number of participants, and rationale

The participants in this clinical trial will be patients with non-acute low back pain of at least 3 weeks' duration who are selected for the study according to the following inclusion and exclusion criteria.

### 1) Inclusion criteria (Inclusion Criteria)

- ① Age: 19 years or older and 70 years or younger at the time of consent.
  - ② Patients with non-acute low back pain (symptom duration  $\geq 3$  weeks) whose average low back pain intensity during the past week is **Numeric Rating Scale (NRS)  $\geq 4$** .
  - ③ Patients in whom **Chuna spinal malposition** has been confirmed on plain radiographs.
  - ④ Patients who voluntarily agree to participate in the clinical trial and sign the **written informed consent form**.
- 

### 2) Exclusion criteria (Exclusion Criteria)

- ① Patients diagnosed with serious specific diseases that can be the cause of low back pain (e.g., spinal metastasis of tumors, acute fracture and spinal dislocation, scoliosis of moderate or greater severity).
- ② Patients with structural abnormalities of the lumbar spine (sacralization, lumbarization), those with a prior history of osteoporosis, or those in whom fracture of the lumbar spine is suspected.
- ③ Patients who are within 3 months after lumbar spine surgery.
- ④ Patients with other chronic diseases that may interfere with the treatment effect or with interpretation of the study results (e.g., chronic renal failure), as judged by the investigator.
- ⑤ Patients with progressive neurological deficits or serious neurological symptoms such as cauda equina syndrome.
- ⑥ Patients who have internal fixation or stabilizing devices in the lumbar spine due to previous lumbar surgery.
- ⑦ Patients with contraindications to interferential current therapy (ICT), such as cancer-related pain or an implanted pacemaker.

- ⑧ Patients who are currently taking systemic steroids, immunosuppressants, psychiatric medications, or other drugs that may affect the study results, as judged by the investigator.
- ⑨ Patients who have received Chuna therapy within the past week, or who have received strong opioid analgesics, anesthetic agents, or invasive treatments such as acupuncture or injection therapy during that period.
- ⑩ Patients who have received nerve block procedures to the lumbar region within the past 2 months.
- ⑪ Patients who are pregnant, breastfeeding, or planning pregnancy during the study period.
- ⑫ Patients who are scheduled, during the 4-week treatment period, to undergo surgery, procedures, or pharmacologic treatment that may affect evaluation of the study results, without this being under the direction of the study physician.
- ⑬ Any other individuals whom the investigator judges to be inappropriate for participation in the clinical trial.
- 

### 3) Number of participants and rationale

#### (1) First pilot clinical study

- **Total number of participants:** 46 (multicenter recruitment)
  - Catholic Kwandong University International St. Mary's Hospital: 12 participants
  - Wonkwang University Korean Medicine Hospital: 34 participants
- **Planned number of participants and interventions by group**

| Group | Planned number of participants | Planned interventions                                       |
|-------|--------------------------------|-------------------------------------------------------------|
| I     | 23                             | Usual care (ICT + exercise guidance) + Chuna manual therapy |
| II    | 23                             | Usual care (ICT + exercise guidance)                        |

#### (2) Rationale for the number of participants in the pilot clinical study

##### ☐ Analysis of previous studies

The sample size for this study was calculated based on the results reported in a previous similar clinical study, using **Cohen's effect size**.

In the previous study, the change in low back pain NRS score in the **Chuna + usual care group** was  $3.02 \pm 1.72$ , whereas in the **usual care group** it was  $1.36 \pm 1.75$  ( $p < 0.001$ ). Based on these data, the effect size (Cohen's  $d$ ) was calculated to be  $d = 0.96$ .

Assuming a two-tailed test, significance level  $\alpha = 0.05$ , and statistical power  $(1 - \beta) = 80\%$ , the following formula was used:

$$n = 2 \times [(Z_{\{\alpha/2\}} + Z_{\beta})^2 / d^2]$$

Here,  $Z_{\{\alpha/2\}}$  is the Z value for a two-sided test at significance level 0.05 (1.96), and  $Z_{\beta}$  is the Z value for 80% power (0.84).

The calculation indicated that the **minimum required sample size per group is 18 participants**.

Taking into account an anticipated **20% dropout rate** during the study, the final target sample size was set at **23 participants per group**, resulting in a total of **46 participants** to be enrolled.

## 6. Study period

- Study period: From the IRB approval date to 31 December 2026.

## 7. Study methods

- **Total number of participants:** 23 participants  $\times$  2 intervention groups = **46 participants** in total.
- **Group-specific planned number of participants and interventions**

| Group | Planned number of participants | Planned interventions                                                    |
|-------|--------------------------------|--------------------------------------------------------------------------|
| I     | 23                             | Usual care (ICT + exercise + lifestyle education) + Chuna manual therapy |
| II    | 23                             | Usual care (ICT + exercise + lifestyle education)                        |

<Study Flow chart>

A schematic diagram of the study flow is provided in the **Study Flowchart (Figure)**.

## Enrollment

- Decision to participate in the clinical trial
- Screening test
- Randomization ( $n = 46$ ) (*0 weeks*)

## Allocation

- Usual care + Chuna manual therapy (n = 23)
- Usual care (n = 23)

## Treatment period

(2 times/week × 4 weeks)

1. Usual care
  - Interferential current therapy (ICT) + exercise guidance
2. Chuna manual therapy
  - Chuna manual therapy based on malposition diagnosis

## Follow-up

- 8 weeks

## Analysis / Follow-up

- Data collection and trial outcomes assessment

### 1) Assignment of subject numbers (Randomization)

- For individuals who have provided **written informed consent** to participate in the clinical trial, a **screening number** is assigned in the order of outpatient visits at screening, as follows:
  - Catholic Kwandong University International St. Mary's Hospital: CK-S001, CK-S002, ...
  - Wonkwang University Korean Medicine Hospital: WK-S001, WK-S002, ...
- After the screening tests, participants who meet the selection criteria and do not meet any exclusion criteria are finalized as study subjects.
- After subject selection, **one person among the research personnel** who is not involved in treatment or assessment and **does not pose any risk of influencing the study results or their analysis** is designated as **unblinded**.
- This unblinded person opens, in order, the **opaque allocation envelopes** prepared based on a **block randomization list** generated by an independent statistician, and assigns a **randomization number** to each participant as follows:
  - Catholic Kwandong University International St. Mary's Hospital: CK-R001, CK-R002, ...
  - Wonkwang University Korean Medicine Hospital: WK-R001, WK-R002, ...
- A single participant cannot be assigned **more than one** randomization number, and each randomization number is assigned to **only one** participant.
- For each participant, the combination of the screening number, randomization number, and initials is used as the **subject identification code** to identify the participant until the end of the clinical trial.

- The randomization list allocates participants to the **usual care + Chuna group (Group I)** and the **usual care-only group (Group II)** in a **1:1 ratio**. The randomization table is generated by an independent professional statistician, and the randomization envelopes are also prepared by a third party not involved in the study.

## 2) Blinding and unblinding

Due to the nature of the treatment interventions and study design in this clinical trial, it is not feasible to blind the clinical investigators and participants to group allocation. Instead, outcome assessors will remain blinded in order to minimize bias in the evaluation of participants. Because the clinical investigators and participants are not blinded, no specific unblinding procedure is planned.

## 3) Outline of treatments in each group (summary)

- **Usual care (both groups)**
  - Interferential Current Therapy (ICT) applied to the painful lumbar region for **15 minutes per session**,
  - **Exercise guidance** (pelvic tilt, trunk rotation without weight bearing, knee-to-chest, partial curl-ups, etc.) for about **15 minutes** at each visit,
  - **Lifestyle education** and patient education materials on postures that help prevent low back pain and appropriate working postures.

→ Provided **twice per week for 4 weeks (total 8 sessions)** in both groups.
- **Chuna manual therapy (Group I only)**
  - In addition to usual care, standardized Chuna manual therapy is applied according to the **radiograph-based Chuna malposition diagnosis** confirmed at screening.
  - Techniques are selected according to the SOP for each malposition pattern (simple malposition, specialized techniques for simple malposition, simple techniques for complex malposition, specialized techniques for complex malposition).
  - Chuna therapy is provided **twice per week for 4 weeks (total 8 sessions, about 15 minutes per session)**.
  - Whenever necessary, ultrasound is used before treatment to confirm the exact vertebral level and mark the skin contact point.

## 4) Permitted concomitant medications and precautions

In principle, during the clinical trial period, no medications other than the trial interventions provided within this study should be administered. However, because this is designed as a pragmatic clinical trial, **rescue medications** may be administered at the discretion of the principal investigator when they are deemed necessary for the management of adverse events, pain control, and similar clinical needs.

If a concomitantly administered medication is expected to affect the pharmacodynamic evaluation or safety assessment of this trial, the corresponding participant will be withdrawn from the study (for permitted rescue medications, see **Section 13. Rescue medication**).

All concomitant medications and the reasons for their use must be documented in the source documents and the case report form (CRF), and signed by the principal investigator or sub-investigator. For any other medications, participants must be instructed to **consult the study team before taking the medication**.

---

## 8. Observation and examination items

### 1) Screening visit (Visit 1, Day -7 to Day 0)

Screening to assess eligibility will be carried out **only in participants who have signed the written informed consent form**. Participants in whom clinically significant abnormalities are identified on the following assessments will be excluded.

(If eligibility is confirmed at the screening visit, the baseline tests may be conducted on the same day.)

#### (1) Demographic information

- Sex, age, height, weight, BMI, smoking history, alcohol consumption.

#### (2) Medical history

- Duration of low back pain, current medications, past medical history.

#### (3) Physical examination and vital signs

- Medical interview and physical examination of general condition, nutritional status, skin/mucosa, eyes, ear-nose-throat, thyroid, lungs, heart/circulatory system, abdomen, kidneys/urogenital system, nervous/psychiatric system, spine/limbs/tumors, peripheral circulation, and lymphatic system.
- Vital signs: blood pressure (sitting), pulse rate, body temperature.  
Blood pressure and pulse are measured **after at least 5 minutes in the sitting position without abrupt postural changes**.

#### (4) Imaging examination and assessment of Chuna malposition

① Lumbar spine AP and lateral standing radiographs (L-spine AP & lateral standing view) will be obtained according to the Chiropractic Biophysics standardized

procedures described in **Section 6–1, Radiograph–based Chuna diagnostic method used in the clinical trial.**

② Based on the imaging DICOM files, the presence and type of Chuna spinal malposition will be determined.

#### (5) Confirmation of inclusion/exclusion criteria

- Final judgement of inclusion and exclusion criteria will be made by reviewing NRS scores, existing medical history, and prior treatment history.

---

## 2) Baseline visit (Visit 2, Day 0)

(Visit 1 and Visit 2 may be performed on the same day.)

For patients who pass the screening test and are enrolled in the clinical trial, **block randomization** will be performed, a subject number will be assigned, and the following assessments will be carried out:

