### (1) Questionnaires on subjective symptoms, functional limitation, and quality of life

- Numeric Rating Scale (NRS) – assessed separately for low back pain and leg pain.
- Oswestry Disability Index (ODI).
- European Quality of Life 5 Dimension (EQ-5D)–5L.
- Roland–Morris Disability Questionnaire (RMDQ).

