### 14. Efficacy and safety evaluation

#### 14.1 Efficacy evaluation

##### ☐ Primary efficacy outcome

- The **primary efficacy outcome** of this clinical trial is the **change in low back pain intensity** measured by the **Numeric Rating Scale (NRS)**.
- NRS for low back pain is assessed at **baseline (week 0)**, **end of treatment (week 4)**, and **follow-up (week 12)**, and the change from baseline at each time point is compared between the two groups.

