### a. Analysis of the primary efficacy outcome

- For each measurement time point, changes in the **NRS score for low back pain** from baseline (week 0) to the end of treatment (week 4) and follow-up (week 12) will be summarized for each treatment group using descriptive statistics (number of participants, mean, standard deviation).
  - For within-group tests of the change in NRS for low back pain (from baseline to week 4):
    - If the normality assumption is satisfied, a **paired t-test** will be used.
    - If the normality assumption is not satisfied, a **Wilcoxon signed-rank test** will be used.
  - To evaluate the effect of the treatment group compared with the control group, an **ANCOVA model** will be used, with:
    - the **treatment group** as a fixed effect, and
    - the **baseline NRS score** as a covariate, analyzing the change in NRS from baseline to the end of treatment (week 4).
  - The **least-squares mean (LSM) difference** between the treatment and control groups, the **two-sided 95% confidence interval** for this difference, and the **p-value** will be presented.
- 

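### Visit 2 lists randomisation ahead of the self-reported baseline scores, and nothing requires those scores to be recorded before unblinded participants can learn their arm

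*Protocol*

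**What the plan says.** Protocol section 8, 2) Baseline visit (Visit 2, Day 0) names block randomisation first. The rest of the sentence reads "will be performed, a subject number will be assigned, and the following assessments will be carried out". The list that follows contains the NRS, "assessed separately for low back pain and leg pain", then ODI, EQ-5D-5L and RMDQ, and then lumbar range of motion.

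Section 7, 1) Assignment of subject numbers ties the envelope to eligibility: "After the screening tests, participants who meet the selection criteria and do not meet any exclusion criteria are finalized as study subjects". The unblinded person then opens the next envelope. No baseline questionnaire is a condition of opening it. The flow chart places randomisation after the screening test, at week 0.

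Section 7, 2) Blinding and unblinding states that "it is not feasible to blind the clinical investigators and participants to group allocation". Only the outcome assessors are blinded.

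The week-0 value is used in three places:
- Section 14.1, primary outcome: "the change from baseline at each time point is compared between the two groups".
- Section 15, 2) a: ANCOVA of the change to week 4, with baseline NRS as covariate.
- Section 14.1, item 5, and section 15, 2) d: responders are defined by a fall of at least 2 NRS points from baseline.

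An NRS also exists before randomisation. Section 6 requires past-week average low back pain of at least 4, and section 8, 1) (5) says: "Final judgement of inclusion and exclusion criteria will be made by reviewing NRS scores, existing medical history, and prior treatment history". Nothing names that score as the analysis baseline.

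**The concern.** A baseline belongs before allocation, so that it cannot depend on the arm. Here the comparison is usual care against the same usual care plus Chuna, and participants know what they receive. Someone who has just learned the arm may rate pain differently through disappointment or expectation. Assessor blinding gives little protection, because the participant is the one who rates NRS, ODI, EQ-5D-5L and RMDQ.

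If the recorded baseline differs between arms because of allocation, the whole difference enters the raw change score, the within-group tests and the responder rule. ANCOVA rests on a covariate that treatment assignment has not affected. When that fails, adjustment reduces the error but does not remove it.

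**Working it through.** **Planned difference (section 6, 3) (2)).** Changes are 3.02 (SD 1.72) and 1.36 (SD 1.75).
- Difference: 3.02 − 1.36 = 1.66 points.
- Pooled SD: √((1.72² + 1.75²)/2) = 1.735, so d = 1.66/1.735 = 0.957; the plan states 0.96.
- Per group: 2 × (1.96 + 0.84)²/0.96² = 17.01, rounded up to 18; 18/0.8 = 22.5, rounded up to 23.

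The plan's figures reproduce and are not in dispute. They serve here as a yardstick.

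**Bias formulas.** Let s be the between-arm difference in recorded baseline caused by knowing the arm, and β the slope of week-4 NRS on baseline NRS. Neither is in the documents. I assume s = 0.5 or 1.0 points and β = 0.3 to 0.7.
- Raw change (baseline minus week 4): bias = s.
- ANCOVA of change on arm and recorded baseline: bias = β × s. This follows because week-4 NRS depends on the unshifted baseline, which equals the recorded baseline minus s in the shifted arm.

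**Numbers for s = 0.5.**
- Raw change: 0.5 points; 0.5/1.66 = 30% of the planned difference.
- ANCOVA: 0.3 × 0.5 = 0.15 to 0.7 × 0.5 = 0.35 points; 0.15/1.66 = 9% and 0.35/1.66 = 21%.

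**Simulation check.** No true effect, 8,000 runs per setting, change SD 1.735, equal SDs at both times (so β equals the correlation), two-sided 5% test, and the shift placed on the baseline rating only.

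| n per group | s | ANCOVA bias, β = 0.3 / 0.5 / 0.7 | ANCOVA type I error, β = 0.3 / 0.5 / 0.7 |
|---|---|---|---|
| 23 | 0 | 0.00 / 0.01 / 0.01 | 4.8% / 4.9% / 4.8% |
| 23 | 0.5 | 0.16 / 0.24 / 0.36 | 6.6% / 8.8% / 10.9% |
| 23 | 1.0 | 0.30 / 0.51 / 0.70 | 10.3% / 19.1% / 29.0% |
| 18 | 0.5 | 0.15 / 0.25 / 0.35 | 5.8% / 7.5% / 9.8% |
| 18 | 1.0 | 0.30 / 0.51 / 0.70 | 9.1% / 15.5% / 22.6% |

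The simulation agrees with β × s. With s = 0 the bias is about zero and the error rate about 5%.

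**Which outcomes are exposed.**
- Fully: low back and leg pain NRS, ODI, EQ-5D-5L, RMDQ and the responder rule.
- Less: range of motion, which section 14.1 has measured with an instrument such as an inclinometer or goniometer, with assessors blinded.
- Not at all: imaging, because section 8, 2) (4) uses the screening radiographs as baseline.

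**The case against.** **The Visit 2 sentence may be a list and not a sequence.** It has no sequencing word, and section 8, 1) ties baseline tests to confirmed eligibility, allowing them on the same day. That is fair: the order is read from how the items are listed and is not commanded. But no section gives the opposite order, and a site that works down the list would randomise first.

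**Knowledge of the arm at the time of rating is not documented.** A reader might infer that participants do rate baseline pain knowing whether they will receive Chuna. The protocol does not say when they are told. The envelope is opened by someone outside treatment and assessment, so a participant could finish the questionnaires before disclosure. This objection stands and limits the point to what can happen. Nothing in the text prevents disclosure first.

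**Not every change score is touched.** Correct, as set out above for imaging and range of motion.

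**A pre-randomisation NRS exists.** A reader might infer that the bias could not be removed in analysis. For low back pain NRS that goes too far, since the screening value can support a sensitivity analysis. ODI, EQ-5D-5L, RMDQ and range of motion have no listed screening value.

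**The magnitude is assumed, and later ratings are unblinded anyway.** Both are true. If the reporting effect persists at week 4 as a fraction k of s, the raw bias becomes s − ks and the ANCOVA bias βs − ks, so the net error differs and may be smaller. The parts due to baseline timing remain s and βs. Unblinded follow-up ratings cannot be avoided in this design, but unblinded baseline ratings can.

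**Conclusion.** The point holds as a weakness in the stated visit procedure. As written, the self-reported baselines, including the one behind the primary change score, the ANCOVA covariate and the responder rule, can be collected after participants know their arm. The documents do not show that this will happen, in which direction it would act, or how large it would be.

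The illustration of 0.5 points on raw change and 0.15 to 0.35 points on the ANCOVA estimate (9% to 21% of 1.66) rests on an assumed 0.5-point shift and an assumed slope of 0.3 to 0.7. The between-group test is the ANCOVA, so 9% to 21% is the relevant range for it; 30% applies to raw mean changes. In a 46-participant pilot with unblinded follow-up ratings this adds to an acknowledged limitation, but it can be avoided at almost no cost.

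**What to change.** Reword section 8, 2) so that at Visit 2 all baseline questionnaires and range of motion are completed and recorded, with the time noted, before the allocation envelope is opened. Make this a condition of opening the envelope in section 7, 1). In sections 14.1 and 15, define baseline as that pre-randomisation value.

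If any participant has been rated after allocation, add a sensitivity analysis with the screening NRS as the baseline covariate. Its response should be the week-4 NRS itself, or change from the screening value. If change from the Visit 2 value stayed as the response, the full shift s would remain in it.

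The cost is re-sequencing one visit and a few sentences of text. The assessments, visit schedule and sample size (18, inflated to 23 per group) do not change.
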